## Abstract

**Background::**

Respiratory disease has emerged as a global issue due to COVID-19. In particular, there has been an increased frequency of occurrence of symptoms such as cough, sputum, and dyspnea, which commonly accompany chronic obstructive pulmonary disease (COPD). *Liriope platyphylla* (LP) extract is known to improve respiratory function. LP extract ameliorates the symptoms commonly seen in bronchitis, asthma, and COPD and enhances immunity, as it has anti-inflammatory properties. In a previous study in rats, LP effectively improved respiratory inflammation levels. However, few randomized controlled trials have verified the effects of LP in respiratory disease and there have been no studies to determine the appropriate dose and duration to make it a more convenient functional health product. Based on previous studies, we would like to proceed with this clinical trial under the assumption that LP will help improve respiratory function and produce anti-inflammatory effects.

**Methods::**

This will be a single-center, randomized, double-blind, placebo-controlled pilot trial. Participants will randomly be allocated to receive either 1000 mg LP or placebo. The total duration of the clinical trial will be 4 to 6 weeks. A follow-up assessment will be conducted 4 weeks after screening, and the effect and safety of LP application will be assessed at this second visit. The primary outcome will be the breathlessness, cough, and sputum scale score. Secondary outcomes will include pulmonary function, clinical symptoms of cough and sputum (reported through a questionnaire), changes in immune cells, changes in immune factors used to analyze allergic inflammation in bronchi, antioxidant enzyme activity, nitric oxide level, and COPD assessment test score.

**Discussion::**

This study has limited inclusion and exclusion criteria and the intervention will be well-controlled. This will be the first randomized controlled trial to assess the efficacy and safety of LP extract in adults with cough and sputum. This study will provide insight into the mechanisms of the anti-inflammatory effects and improvement of respiratory function of LP.

## Introduction

1

Respiratory disease has emerged as a global issue due to COVID-19, which has been prevalent since the end of 2019. In Korea, even before the onset of the COVID-19 pandemic, people were wary of respiratory diseases caused by fine dust. Among air pollutants, fine dust has recently been recognized as the most serious threat to human health.^[1]^ Fine dust affects the respiratory system in particular, as the small size of the particles allows for deposition in the lower bronchial tubes and parenchyma of the lungs, resulting in decreased lung function and increased respiratory symptoms.^[2]^

Bronchial inflammation resulting from fine dust exposure is the most common respiratory disease.^[3]^ The main respiratory symptoms are cough, sputum, shortness of breath, wheezing, and chest discomfort.^[4]^

Accordingly, a need for effective health functional food and medicine products and complementary medicine for respiratory diseases has emerged, and there has been increased interest in and development of products. The monocotyle flowering plant *Liriope platyphylla* (LP) is known to have antioxidant and anti-inflammatory effects^[5,6]^ and immunomodulatory abilities^[7]^ and has been widely used for lung and respiratory diseases. In particular, it is effective for treating bronchitis, pharyngitis, and asthma accompanied by dry cough.^[8,9]^

In this study, LP will be used as a raw material to derive medicine from a natural herbal supplement. The effects of LP on respiratory function, improvement of symptom, and the alleviation of inflammation will be tested.

The following protocol has been designed to verify the safety and efficacy of LP in treating respiratory system symptoms using a single-center, randomized, controlled, and double-blind clinical trial.

## Methods

2

### Study design

2.1

We designed a double-blind, single-center, randomized clinical trial to investigate the efficacy of LP in improving respiratory function. A total of 22 participants with respiratory symptoms (cough, sputum) will be recruited from outpatients at the Daejeon University Cheonan Korean Medicine Hospital (DUCKMH) through advertisements posted on bulletin boards at hospitals. Recruitment commenced in July 2021, and the trial is expected to end in December 2021. All participants will receive a full written explanation of the study protocol and an informed consent form.

Pulmonary function tests will be performed for those with respiratory symptoms, including cough or sputum, based on history or questionnaires. Additionally, blood tests for liver function, inflammation-related cells, and complete blood count will be performed.

A total of 22 participants who meet the eligibility criteria for this study will be randomly assigned in a 1:1 ratio to the treatment group (1000 mg LP) or control group (placebo). The intervention will begin within 2 weeks of the screening visit.

Based on the study group they are randomized into, the participants will be administered either 1000 mg LP or placebo for 4 weeks. The total duration of the clinical trial will be 4 to 6 weeks, and the efficacy and safety will be assessed at the second visit. A flowchart of the study is shown in Figure 1 and Table 1.

**Figure 1 F1:**
[figure not shown]
SPIRIT checklist showing the schedule of enrollment, assessments, and allocation for each subject in the *Liriope platyphylla* extract pilot clinical trial protocol.

**Table 1 T1:** Clinical trial process for the *liriope platyphylla* extract clinical trial protocol.

Item	Screening (–2 wk to 0 d)	Visit 1 (baseline visit) (0 d)	Visit 2 (trial end) (4 wk ± 5d)
Prepare a written consent form	√		
Evaluate inclusion/exclusion criteria	√		
Examine subject information	√		
Assign screening number	√		
Assign random numbers to subjects		√	
Investigate medical history and medication history	√	√	
Assess vital signs	√	√	√
Conduct clinical laboratory blood test	√	√	√
Conduct pregnancy test	√		
Distribute experimental/control foods		√	
Measure effectiveness-evaluation variables		√	√
Check adverse events			√
Identify concomitant drugs			√
Check compliance			√
Confirm cancellation and withdrawal criteria		√	√

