### Sample size calculation

2.4

This study is a pilot trial to explore the effect of LP on the primary and secondary outcome measures selected for a minimum sample size, and to investigate the sample size calculation basis and feasibility for future clinical trials. According to Whitehead et al,^[10]^ when the power is considered to be 80% and effect size is considered moderate, in a preliminary parallel-designed study the empirically optimal sample size is 10 persons per group. As this current study plan includes 2 visits within 4 weeks, high compliance is expected, which suggests a calculated dropout rate of 5%. Therefore, we designed a pilot study involving 22 participants.

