### Intervention

2.6

All eligible participants will receive treatment according to their allocated group (LP or placebo) during the 4-week treatment period. To maintain the double-blinded nature of the study, the 1000 mg LP and placebo will be manufactured to be indistinguishable in appearance by D&L Biochem (Chungju, Republic of Korea). One capsule will be taken orally twice a day. Any other treatment received during their participation in the trial, functional health foods taken, or additional therapies will be considered to be combination therapy. If coadministration is necessary, the administration details will be recorded in the case report form and treatment chart, and the existing therapy will remain unchanged. The participants will be evaluated after 4 weeks.

Concomitant drug administration will however be minimized during trial participation, and will be allowed based on the judgment of the principal investigator when it is deemed inconsequential to the trial. If a drug directly affects immune function, that participant will be withdrawn from the trial.

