### Outcome measures

2.7

The primary outcome is the BCSS score, which will be used to assess respiratory symptoms, such as dyspnea, cough, and sputum. The secondary outcomes are the pulmonary function test (FVC, FEV1, FEV1/FVC), the clinical symptoms of cough and sputum (assessed through a questionnaire), high-sensitivity C-reactive protein level, erythrocyte sedimentation rate, white blood cell count, eosinophil, T cell, B cell, and immune factors (interleukin (IL)-1β, IL-4, tumor necrosis factor (TNF)-α, IL-6, IL-8, interferon (IFN)-γ, immunoglobulin (Ig)E) to analyze allergic inflammation in the bronchi, antioxidants (glutathione peroxidase, superoxide dismutase, nitric oxide) to analyze bronchial peroxide expression levels, and COPD assessment test score. All outcome measures will be assessed at the first and second visits. To ensure the safety of the participant, we will conduct laboratory tests, such as liver function, complete blood count, and electrolytes, and evaluate vital signs at every visit. Safety assessments will be conducted during the second visit. The participants’ data will be anonymized and coded using a specific program (Fig. 2).

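### Table 1 schedules no safety, concomitant-drug, compliance or withdrawal check between dispensing and the final visit: a minor weakness that one day-14 contact plus a change to the withdrawal rules would ease

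*Protocol article*

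**What the plan says.** Table 1 (section 2.1) has three columns: screening, Visit 1 on day 0, and "Visit 2 (trial end) (4 wk ± 5d". Product is distributed at Visit 1 only. The rows for adverse events, concomitant drugs and compliance carry a tick at Visit 2 alone. The row "Confirm cancellation and withdrawal criteria" is ticked at Visits 1 and 2.

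The text agrees with the table. Section 2.1 states that "the efficacy and safety will be assessed at the second visit", and section 2.7 that "Safety assessments will be conducted during the second visit". Efficacy follows the same pattern: "All outcome measures will be assessed at the first and second visits". Section 2.11 has side effects assessed at every visit, but only Visit 2 comes after dosing. Section 2.4 gives a reason for the light schedule: "As this current study plan includes 2 visits within 4 weeks, high compliance is expected".

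Several rules remove participants during the trial. Section 2.6 is mandatory: "If a drug directly affects immune function, that participant will be withdrawn from the trial". Section 2.11 requires withdrawal after a serious adverse event, which goes to the review board within 24 hours of being identified. Section 2.10 is discretionary on interfering medicines or health foods and on pregnancy. Section 2.6 also says that concomitant drugs "will be allowed based on the judgment of the principal investigator when it is deemed inconsequential to the trial". Section 2.9 fills missing values by last observation carried forward.

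**The concern.** The withdrawal rules and the 24-hour report start only once someone learns of the trigger, and no step is scheduled to find one between day 0 and Visit 2. If a participant starts an immune-acting drug or has an adverse event early in intake and says nothing, the first planned question comes on day 23 to 33. By then intake is over or nearly so, and withdrawal can do little to limit exposure. Likewise, a lapse in compliance is found too late to correct.

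The adverse-event rate is the stated safety result in section 2.9. Without an earlier prompt, it depends on what participants remember over the whole interval. Mild, transient events early in intake are the ones most easily forgotten.

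**Working it through.** **Inputs.** Visit 2 window: 4 weeks ± 5 days (Table 1). Intake: 4 weeks, taken as days 0 to 28 (section 2.1). Per-arm base of 10 and dropout of 5% (section 2.4). Allocation 1:1 (section 2.1). Outcomes at Visits 1 and 2 only (section 2.7). Last observation carried forward (section 2.9).

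**The plan's own figure.** 10 / (1 − 0.05) = 10.53, rounded up to 11 per arm, so 22 in total. This reproduces the stated sample size. The base of 10 comes from a cited source and was not re-derived.

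**Window.** 28 − 5 = day 23; 28 + 5 = day 33.

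**Longest interval without a scheduled check.** As planned it equals the Visit 2 day, V. With a day-14 contact it is max(14, V − 14).

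| Visit 2 day | As planned | With day-14 contact | Shortening |
|---|---|---|---|
| 23 | 23 days | max(14, 9) = 14 | 1 − 14/23 = 39% |
| 28 | 28 days | max(14, 14) = 14 | 1 − 14/28 = 50% |
| 33 | 33 days | max(14, 19) = 19 | 1 − 19/33 = 42% |

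**Intake days left at the first check after dispensing.** As planned: max(0, 28 − V) = 5, 0 and 0 days, that is 0 to 18% of 28 (5/28 = 17.9%). With the contact: 28 − 14 = 14 days, or 50%.

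**What a withdrawal does to the primary outcome.** The only post-baseline value is at Visit 2. If it is missing and the participant stays in the analysis, the carried value is the baseline, so change = baseline − baseline = 0. One such case is 1/11 = 9.1% of an arm.

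This last step bears on the remedy. Under the present schedule, a trigger first found at Visit 2 is found when the participant is there to be measured. A trigger found on day 14, under rules that remove people from the trial, could leave no Visit 2 value. A call added without changing those rules could therefore create missing data.

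**The case against.** The strongest case against is that nothing here is misstated. Sections 2.1, 2.7 and 2.11 agree with Table 1, and section 2.4 shows that two visits were chosen on purpose for a short pilot. Participants are screened for serious renal, hepatic, cardiovascular and lung disease, and section 2.3 reports no toxicity in preclinical work. A condensed article may also leave telephone contacts and reporting instructions to the full protocol.

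Much of this stands. The point is an improvement and does not correct an error. It is more than an article's silence, however, because the article sets out the two-visit schedule and places the safety assessment at the second visit. Unscheduled contact described elsewhere would reduce the concern.

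A reader might infer that nothing watches over participants during intake. The document does not support that. Section 2.6 puts concomitant drugs under the investigator's judgment, section 2.11 says subjects are monitored for untoward symptoms, and section 2.5 provides for disclosing an allocation after a serious event. What these provisions lack is a scheduled contact, so they work only if the participant asks or reports.

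It is also fair to object that a call cannot simply be added with the withdrawal rules left alone. Sections 2.6, 2.10 and 2.11 take people out of the trial, and the working above shows the consequence. That objection is accepted, and the fix changes those rules too.

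**Conclusion.** The point holds as a minor, mainly safety-related design weakness. All 22 participants have no scheduled check of the four items from dispensing until day 23 to 33. Detection during intake relies on unprompted reporting, and the adverse-event rate relies on recall over up to 33 days.

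The 39 to 50% shortening describes the spacing of checks and nothing else. A reader might take it as a gain in data quality or in the trial's results. The document gives no event rate or under-reporting rate from which such a gain could be derived, and no benefit to the immune-marker outcomes is claimed. Sample size, significance level and the primary rank-sum test do not change.

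The conclusion assumes that intake runs from day 0 to day 28 and that no contact beyond Table 1 is scheduled. The zero-change figure further assumes that a participant without a Visit 2 value stays in the analysis.

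**What to change.** Two changes, made together:

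1. Add one remote contact (telephone or message) at about day 14 to Table 1, ticked for adverse events, concomitant drugs, compliance and withdrawal criteria.
2. Amend sections 2.6, 2.10 and 2.11 so that a participant who meets a withdrawal criterion after randomization stops product but, unless consent is withdrawn, still attends Visit 2 for outcome and safety measurement. Carrying the baseline forward then does not replace a value that could have been obtained.

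The cost is about 22 short calls by existing staff and a small protocol amendment with review-board approval. No extra on-site visit or laboratory test is needed. There are downsides. The contact yields self-report only, with no capsule count, laboratory result or pregnancy test. It may slightly prompt adherence and event reporting in both blinded arms. Some participants may stop product earlier, so some Visit 2 values will be measured off product.

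Section 2.1 expected the trial to end in December 2021. If it is complete, the change belongs in the later trial that this pilot is meant to inform.

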### Inclusion and exclusion criteria

2.2

The inclusion criteria are as follows:

1.age 19 to 80 years;2.persistent respiratory symptoms (cough, sputum);3.forced expiratory volume in 1 second (FEV1)/forced vital capacity (FVC) level, above 70%; and4.provision of written consent to participate in the trial.

The exclusion criteria are as follows:

1.past or present history of respiratory diseases (respiratory diseases involving damaged lung parenchyma, such as tuberculosis or bronchiectasis; inflammatory lesions in the lung parenchyma due to pneumonia or tuberculosis; undergoing treatment for bronchial asthma, COPD, influenza, pneumonia, or lung cancer; acute or chronic bronchitis with breathlessness, cough, and sputum scale score (BCSS) >9 and persistent cough or sputum for at least 3 months per year for 2 consecutive years);2.uncontrolled cardiovascular disease;3.use of systemic corticosteroids, immunosuppressants, health functional foods, or medicine to control the respiratory system in the 4 weeks prior to the study;4.serum creatinine > 2 mg/dL, or on dialysis for chronic kidney failure;5.total bilirubin ≥2 mg/dL, or aspartate aminotransferase or alanine aminotransferase blood levels ≥3 times the normal upper reference limits;6.uncontrolled psychological disease or alcoholism;7.participation in interventions in other clinical trials within 1 month of the screening visit;8.pregnant or breastfeeding; and9.unsuitability for this study (as determined by the investigator) based on overall health status.

### Dosage calculation

2.3

We have previously demonstrated in both *in vitro* and *in vivo* experiments that LP improves inflammation and shows no toxic effects. To determine the minimum effective concentration, LP was administered at 200 mg/kg to mice for 14 days. Based on the United States Food and Drug Administration guidelines for calculating the effective dose according to body surface area in humans, the effective dose in the animal tests was used to calculate the effective dose in terms of the human body. The human dose was set at 960 mg. For this study, the dose was set at 1000 mg in consideration of the ease of production and intake.

### Sample size calculation

2.4

This study is a pilot trial to explore the effect of LP on the primary and secondary outcome measures selected for a minimum sample size, and to investigate the sample size calculation basis and feasibility for future clinical trials. According to Whitehead et al,^[10]^ when the power is considered to be 80% and effect size is considered moderate, in a preliminary parallel-designed study the empirically optimal sample size is 10 persons per group. As this current study plan includes 2 visits within 4 weeks, high compliance is expected, which suggests a calculated dropout rate of 5%. Therefore, we designed a pilot study involving 22 participants.

### Randomization and blinding procedures

2.5

Randomization will be performed using the block randomization method in the experimental and control groups at a ratio of 1:1. The size of the block will be set randomly by a statistician. Subjects who meet all the registration criteria will be randomly assigned a randomization identification code (e.g., DLB-R-001, DLB-R-002, …, DLB-R-022) in the order generated by a computer-randomized program. The randomization number will be given to each participant and will indicate whether 1000 mg LP or placebo is to be given. As this pilot study was designed to be double-blinded, the participants, researchers, and assessors collecting the data will be blinded to the group allocation. Information on the intervention assignment will be stored in the statistical department. The randomization code will be placed in an opaque envelope and stored in the hospital. With the exception of disclosure of an individual patient's status in the case of a serious adverse event, randomization and blinding will not be disclosed to researchers until the end of the trial.

### Intervention

2.6

All eligible participants will receive treatment according to their allocated group (LP or placebo) during the 4-week treatment period. To maintain the double-blinded nature of the study, the 1000 mg LP and placebo will be manufactured to be indistinguishable in appearance by D&L Biochem (Chungju, Republic of Korea). One capsule will be taken orally twice a day. Any other treatment received during their participation in the trial, functional health foods taken, or additional therapies will be considered to be combination therapy. If coadministration is necessary, the administration details will be recorded in the case report form and treatment chart, and the existing therapy will remain unchanged. The participants will be evaluated after 4 weeks.

Concomitant drug administration will however be minimized during trial participation, and will be allowed based on the judgment of the principal investigator when it is deemed inconsequential to the trial. If a drug directly affects immune function, that participant will be withdrawn from the trial.

### Outcome measures

2.7

The primary outcome is the BCSS score, which will be used to assess respiratory symptoms, such as dyspnea, cough, and sputum. The secondary outcomes are the pulmonary function test (FVC, FEV1, FEV1/FVC), the clinical symptoms of cough and sputum (assessed through a questionnaire), high-sensitivity C-reactive protein level, erythrocyte sedimentation rate, white blood cell count, eosinophil, T cell, B cell, and immune factors (interleukin (IL)-1β, IL-4, tumor necrosis factor (TNF)-α, IL-6, IL-8, interferon (IFN)-γ, immunoglobulin (Ig)E) to analyze allergic inflammation in the bronchi, antioxidants (glutathione peroxidase, superoxide dismutase, nitric oxide) to analyze bronchial peroxide expression levels, and COPD assessment test score. All outcome measures will be assessed at the first and second visits. To ensure the safety of the participant, we will conduct laboratory tests, such as liver function, complete blood count, and electrolytes, and evaluate vital signs at every visit. Safety assessments will be conducted during the second visit. The participants’ data will be anonymized and coded using a specific program (Fig. 2).

**Figure 2 F2:**
[figure not shown]
Study design for LP clinical trial. The treatment or control groups will be administered. LP 1000 mg or placebo. The subjects will receive LP 1000 mg or placebo for 4 weeks and will visit 2 times.

### Data collection

2.8

During screening, the participants will complete a questionnaire regarding their sociodemographic characteristics and provide a history of respiratory disease within the past 2 years, their medical history of the last 3 months, and their drug history of the previous 4 weeks. Lung function tests, laboratory tests for liver function, complete blood counts, immune function assessment, and inflammatory factor assessments will also be conducted. Personal information and data collected during the screening period will be managed by the hospital. The final dataset will be accessible to statisticians and key investigators. The results of this study will be published in a peer-reviewed journal.

Personal information will be collected during screening. The investigator will process the data, including personal information, under the clinical study protocol approved by the institutional review board (IRB). The participants’ names will remain confidential and participants will be identified only by their assigned randomized number.

The investigator will secure the data, including personal information, in locked cabinets. Access to the data will be restricted. All data will be handed to the storage manager after the clinical trial results have been reported, and the data will be preserved for 3 years from the date of completion of the trial.

